### 6.4. Population and Eligibility Criteria

Three different populations will be considered and compared.
-Subgroup 1: Patients with initial histological diagnosis from prostate biopsy of PCa considered for radical prostatectomy as primary therapy, as a therapeutic choice shared with the doctor and in accordance with international guidelines. This treatment will follow normal clinical practice for this pathology and regular clinical and therapeutic procedure. Staging of these patients will be non-metastatic PCa at imaging (multiparametric magnetic resonance of the prostate).-Subgroup 2: Patients with initial histological diagnosis from prostate biopsy of advanced metastatic PCA (mHSPC) to be subjected to standard pharmacological treatments with androgen deprivation (ADT) and new androgen-targeted treatments (ARPI) or chemotherapy with taxanes, as a therapeutic choice shared with the doctor and in accordance with international guidelines. This treatment will follow normal clinical practice for this pathology and regular clinical and therapeutic procedure. Staging of these patients will be metastatic at imaging (PET CT scan or bone scan and CT scan).-Subgroup 3: Patients with initial diagnosis of BPH who have not undergone treatments. A healthy control population is not included but the BPH population will be used as a control. The clinical comparison will use male subjects of the same age (40–75 years) to determine the expression of a potential marker for prostatic neoplasia, involving the evaluation of differences within a population with benign prostatic pathology such as BPH and not healthy subjects (those without BPH) of mismatched age.

#### 6.4.1. Subgroup 1 and 2

Inclusion criteria: Male patients aged between 40 and 75 years, of any ethnicity, with an initial histological diagnosis of PCa from prostate biopsy. Non-metastatic versus metastatic clinical stage, intermediate or high-risk class according to d’Amico, indication as primary treatment for radical prostatectomy (Subgroup 1) or systemic therapy with androgen deprivation and ARPI or taxanes (Subgroup 2).

Exclusion criteria: Local or systemic therapies for PCa, other neoplasms in the active phase or undergoing treatment, ongoing oncological therapies (chemotherapies, target therapies, radiotherapies), hormonal or steroid therapies in progress or with drugs known to interfere with the evaluation foreseen in the study.

#### 6.4.2. Subgroup 3

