Inclusion criteria: male patients aged between 40 and 75 years, of any ethnicity, with an initial diagnosis of BPH.

Exclusion criteria: local or systemic therapies for BPH, suspicion or diagnosis of prostatic neoplasia, other neoplasms in the active phase or undergoing treatment, ongoing oncological therapies (chemotherapies, target therapies), hormonal or steroid therapies in progress or with drugs known to interfere with the assessment intended for the study.

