Metabolites will instead be analyzed by an untargeted metabolomic approach. Before analysis, Quality Control (QC) samples will be prepared for further instrumental system conditioning and sample normalization over time. Data acquisition for samples, controls, and QCs will be obtained by ultra-high-performance liquid chromatography coupled with untargeted high-resolution mass spectrometry (UHPLC-HRMS). A data acquisition worklist will comprehend a QC run every 5 sample runs for subsequent QC-based normalization. At the end of the data acquisition worklist, a series of QCs will run in data-dependent acquisition tandem mass spectrometry (MS/MS) for subsequent tentative compound identification. All samples will be acquired in positive and negative ion mode for maximum compound coverage. After raw data collection, pre-processing analysis using Compound Discoverer software on samples, controls, and QCs will be needed to extract the *m*/*z* from the raw files, to align the variables (features) among all acquired runs, normalize each feature over time, and remove contaminants present in the blank sample. After data pre-processing, a data matrix will be obtained for further statistical analysis. Features that will be selected from statistical analysis as putative biomarkers will be then tentatively identified by matching the experimental MS/MS spectra to those present in databases, such as the Human Metabolome Database (HMDB), Lipid Maps, Kyoto Encyclopedia of Genes and Genomes (KEGG pathway) and Metabolika. Lipidomics will be carried out using a similar approach to metabolomics, but all instrumental parameters will be adjusted to lipids, including chromatography (C8 column, mobile phases, and gradient), MS tuning and parameters (*m*/*z* range and injection time), and pre-processing and identification tools (Figure 2).

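### Controls must be untreated for BPH, but the cancer groups' exclusion list names no BPH therapy, so some BPH-treatment signals can enter the primary PCa-versus-BPH model only through cases

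*Protocol article*

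**What the plan says.** All places are in section 6 of the protocol article.

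- **Controls (6.4 and 6.4.2).** Subgroup 3 is defined as "Patients with initial diagnosis of BPH who have not undergone treatments". Its exclusion list repeats the bar: "Exclusion criteria: local or systemic therapies for BPH, suspicion or diagnosis of prostatic neoplasia". It then excludes "hormonal or steroid therapies in progress or with drugs known to interfere with the assessment intended for the study".
- **Cases (6.4.1).** The shared list for Subgroups 1 and 2 begins "Exclusion criteria: Local or systemic therapies for PCa, other neoplasms in the active phase or undergoing treatment, ongoing oncological therapies" and ends with "hormonal or steroid therapies in progress or with drugs known to interfere with the evaluation foreseen in the study". BPH drugs and earlier BPH procedures are not named.
- **Role of the BPH group (6.4).** "A healthy control population is not included but the BPH population will be used as a control".
- **Primary comparison (6.3.2).** The first primary endpoint is a diagnostic model separating PCa from BPH, built on proteomic, metabolomic and lipidomic data from the coronas.
- **Assay and pre-processing (6.5).** Metabolites are measured by an untargeted method. The one feature-removal step described is to "remove contaminants present in the blank sample". Features picked out by the statistical analysis are tentatively identified against databases afterwards.
- **Model (6.6).** Unsupervised PCA is followed by PLS-DA for metabolites. OPLS-DA is used for proteins.

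**The concern.** In a case-control comparison, any background factor barred on one side and allowed on the other becomes a marker of group membership. Here that factor is BPH treatment. A man with PCa who takes a non-hormonal drug or a plant extract for urinary symptoms, or who once had a prostate procedure for BPH, is not excluded by any named criterion. The same man without cancer cannot be a control.

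An untargeted assay can record a drug or its metabolites as features. A supervised method looks for whatever separates the labels and cannot tell a drug from a cancer biomarker. The first primary endpoint could therefore look better than the biology supports. In later use, treated men with BPH could be pushed towards a cancer call. The article aims to separate BPH from PCa in general, and it chose BPH men of the same age so that controls would be comparable. A one-sided treatment rule works against both aims.

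**Working it through.** The document gives no group size, error rate, power or rate of BPH treatment, so there is no stated figure to reproduce. The check has two parts.

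**1. The two exclusion lists side by side**

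| Item | Subgroups 1 and 2 (cases) | Subgroup 3 (controls) |
|---|---|---|
| Therapy for the index disease | PCa therapy barred | BPH therapy barred |
| BPH therapy, local or systemic | not named | barred |
| Past BPH treatment | not named | barred (defined as untreated) |
| Other active neoplasms, oncological therapy | barred | barred |
| Hormonal or steroid therapy in progress, interfering drugs | barred | barred |

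Each group is screened for treatment of its own disease. That seems natural, but only the controls are free of BPH treatment by rule. The last row is common to both lists and may take some current BPH drugs out of the case groups, namely those counted as hormonal or judged to interfere. It names no BPH drug, and as a clause about drugs it does not reach a past procedure.

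**2. How large the effect could be (illustration, all inputs assumed)**

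Let p be the fraction of cases with a BPH-treatment feature, counted after the shared clause has been applied. The fraction in controls is 0 by rule. For one binary, perfectly detected feature:

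- sensitivity = p and specificity = 100%
- AUC = p × 1 + (1 − p) × 0.5 = 0.5 + p/2

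| p | AUC |
|---|---|
| 5% | 0.525 |
| 10% | 0.55 |
| 20% | 0.60 |
| 30% | 0.65 |
| 40% | 0.70 |

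The next question is whether such a feature would stand out. With n per group, k treated cases and no treated controls, the two-sided Fisher p-value is 2 × C(n,k)/C(2n,k). At n = 50 this is 0.056 for k = 5 and 0.027 for k = 6. At n = 30 it is 0.052 and 0.024, and at n = 100 it is 0.059 and 0.029. At each of these sizes six treated cases are enough, so the chance of reaching p < 0.05 is the binomial probability of six or more:

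| p | n = 30 | n = 50 | n = 100 |
|---|---|---|---|
| 10% | 7% | 38% | 94% |
| 20% | 57% | 95% | 100% |
| 30% | 92% | 100% | 100% |

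If the same rule held on both sides, the feature would have equal prevalence in cases and controls, its AUC would be 0.50, and it would say nothing about the label.

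**Limits of the illustration.** BPH drugs are several compounds with separate features, so p is split among them. Detection will not be perfect. PLS-DA combines many variables and does not screen one feature at a time at 0.05. The figures are upper bounds for a single feature and do not predict this trial.

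**The case against.** The strongest case on the other side has five parts.

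- **The shared clause may already cover BPH drugs.** If a BPH drug disturbs the assay, it can fairly be called an interfering drug and barred in cases. The separate BPH line for controls does not prove otherwise, because both lists contain overlapping items. This stands in part. A reader might infer that every BPH treatment is open to cases, and the text does not support that. Nor does it settle that non-hormonal drugs are barred, and past procedures are not clearly reached.
- **A drug could be recognised at identification.** Section 6.5 matches selected features to databases. But this comes after selection, is described as tentative, and is followed by no stated removal. It may reveal a drug without keeping it out of the model.
- **The drug-peak route covers only part of the endpoint.** Proteins are searched against a human protein database, and lipidomics is tuned to lipids. Nothing in the article shows that BPH drugs adsorb detectably to these liposomes. This stands: the route bears mainly on the untargeted metabolomic layer. A broader effect on the corona is possible, since section 3 says corona analysis could detect protein changes after treatment and reports that comorbidity altered corona composition. Neither statement concerns BPH treatment.
- **The figures can be over-read.** A reader might infer that the model's AUC will be inflated by p/2, or that false positives in later use will rise by the full share of treated men. The first needs one perfectly detected feature shared by all treated cases. The second needs that feature alone to decide the class. The document supports neither.
- **Drug recording and feature filtering belong in a fuller document.** Agreed, and their absence is not the point here. The point is the eligibility rule, which this article states for each group. An analysis plan cannot supply treated controls whom the protocol bars.

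**Conclusion.** The concern holds in limited form. As written, BPH treatments not caught by the shared drug clause can appear in cases and never in controls. The direction of the resulting signal is fixed by the eligibility rule: it points towards cancer. It falls on the first primary endpoint, mainly through the metabolomic layer and possibly through the corona profile.

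The size cannot be given. It rests on the unknown share of cases with such treatment and on whether the treatment leaves a detectable trace. Under the illustration, the bias is small if few cases are treated and becomes material from about 20% upward. This should be corrected before recruitment. It does not by itself make the comparison unusable.

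**What to change.** **Preferred.** Apply the same BPH-therapy rule to both sides of the primary comparison by aligning the two exclusion lists, with wording that covers past BPH procedures as well as drugs. The cost is one line in the eligibility criteria and slightly slower recruitment of cases.

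**If recruitment cannot bear that.** Do all three of the following:

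1. Record BPH drugs and past BPH procedures at the blood draw.
2. Remove features matched to those drugs and their metabolites from the data matrix before PCA, PLS-DA or OPLS-DA.
3. Report the PCa-versus-BPH model restricted to cases with no BPH therapy. This step is needed because deleting drug features cannot remove the effect of a past procedure.

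The cost is a history field and a little more analyst work.

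**With either.** State that the model's conclusion applies to men untreated for BPH. Neither option brings treated BPH men into the control group, so performance in them remains unstudied.

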### 6.3. Endpoints

#### 6.3.1. Overall Aim

The protocol will aim to develop and implement sensitive nanotools with two distinct objectives. It will carry this out by designing nanoparticles (NPs) capable of selectively binding and detecting biomarkers in order to build a predictive diagnostic model to effectively discriminate between patient sera affected by benign prostatic hyperplasia (BPH) and prostate cancer (PCa). This initiative will be driven by improving diagnostic precision and accuracy, enabling early and accurate differentiation between these two conditions. Secondly, within the population with PCa, in cases of initial advanced metastatic diagnosis (mHSPC = metastatic hormone-sensitive prostate cancer), the objective will be to find biomarkers capable of predicting the response to systemic treatments to improve the precision and efficiency of monitoring treatment outcomes, leveraging the aforementioned nanotechnology and leading to the development of personalized therapeutic strategies for patients.

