### 6.5. Methods

Under a regime of fasting from liquids and solids from midnight the previous evening, in the morning around 8.00 AM a blood sample will be taken from all patients. In Subgroup 1 and 3, the blood sample will be obtained only at baseline. In Subgroup 2, the blood sample will be obtained at baseline before the beginning of therapy and at 3-, 6-, 12-month intervals during systemic therapy. Sample storage will be performed at room temperature for 30 min, followed by centrifugation of the sample (3000× *g*; duration: 15 min) and subsequent separation to obtain a plasma sample. The plasma samples will be transported within 30 min to the chemistry laboratory in a suitable refrigerated container with ice at a temperature of 4 °C after centrifugation of the blood to remove the erythrocytes. As soon as they are delivered to the laboratory, the plasma samples appropriately labeled with the sample identification code will be stored at −80 °C until analysis.

For protein and metabolite corona experiments, in collaboration with the nanodelivery Lab of Sapienza of Rome, we developed a cross-reactive sensor array platform with cancer detection capacity made of three liposomal formulations with different surface charges, i.e., cationic 1,2-Dioleoyl-3-trimethylammonium propane (DOTAP), anionic 1,2-Dioleoyl-sn-glycerol-3-phosphoglycerol (DOPG), and a zwitterionic mixture made of dioleoylphosphatidylcholine (DOPC) and cholesterol [19]

For the proteomics–NP studies, proteins will be identified and quantified by nano-high-performance LC (nanoHPLC) coupled to MS/MS (nanoHPLC−MS/MS). The acquired raw MS/MS data files from Xcalibur software (version 2.2 SP1.48, Thermo Fisher Scientific, Washoe County, NV, USA) will be searched against the Swiss-Prot human database using the MaxQuant search engine with the automatic setting for tryptic peptide matching and label-free analysis. For each NP type, a list with all the identified proteins and their relative protein abundance (RPA, a quantitative estimation of their abundance within the protein corona) will be provided. The list of proteins will be utilized to discover new biomarkers associated with the PCa using sensor array technology [20].

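### Eligibility for the PCa-versus-BPH model ties biopsy and suspicion status to case status, so its discrimination may not carry over to men under diagnostic suspicion

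*Protocol article*

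**What the plan says.** **Cases.** Section 6.4 of the Protocol article defines Subgroup 1 as "Patients with initial histological diagnosis from prostate biopsy of PCa considered for radical prostatectomy". Section 6.4.1 requires men in Subgroups 1 and 2 to enter "with an initial histological diagnosis of PCa from prostate biopsy" and lists "intermediate or high-risk class according to d’Amico" among the inclusion criteria.

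**Controls.** Section 6.4 describes Subgroup 3 as "Patients with initial diagnosis of BPH who have not undergone treatments". Section 6.4.2 includes "male patients aged between 40 and 75 years, of any ethnicity, with an initial diagnosis of BPH" and excludes men with "suspicion or diagnosis of prostatic neoplasia". It neither requires a biopsy nor defines suspicion.

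**Blood sampling.** Section 6.5 states: "In Subgroup 1 and 3, the blood sample will be obtained only at baseline". For Subgroup 2, the baseline sample is placed before the start of therapy. The article gives no interval between biopsy and blood draw.

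**Purpose.** The first primary endpoint (section 6.3.2) is a diagnostic model separating histologically diagnosed cancer from BPH. Section 6.3.1 gives the motive as "improving diagnostic precision and accuracy, enabling early and accurate differentiation between these two conditions". Section 6.6 expects predictions of cancer that are better than those of current methods.

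**The concern.** A diagnostic model learns any feature that differs systematically between cases and controls. Here the groups differ by design in two ways besides cancer: cases were biopsied and, by inference, under suspicion, while controls need be neither.

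The planned analysis is exposed to this. Sections 6.5 and 6.6 describe untargeted features, OPLS-DA and PLS-DA, and deliberate use of broad patterns across many predictors. Such a classifier has no means of telling a cancer signal from a signal of suspicion or of recent biopsy. Statistical adjustment cannot help where the groups barely overlap on the adjusting variable, so an analysis plan could not repair it.

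The question of BPH or cancer is put to men in whom cancer is suspected. If benign men under suspicion are kept out of the control group, the study says little about specificity in that setting. At stake is whether the first primary endpoint can support the aim in section 6.3.1 and the expectation in section 6.6.

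**Working it through.** The article states no sample size, accuracy target or AUC, so there is no figure to reproduce. The finding rests on the eligibility text; the arithmetic only illustrates it.

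**Step 1: the criteria side by side.**

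| Feature | Cases (6.4, 6.4.1) | Controls (6.4, 6.4.2) |
|---|---|---|
| Prostate biopsy | required, positive | not required |
| Suspicion of cancer | implied by the diagnostic biopsy | ground for exclusion |
| Reference standard | histology | BPH diagnosis, histology not required |
| Spectrum | intermediate or high risk, or metastatic | untreated BPH |
| Diagnostic-model blood | baseline | baseline |

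Because histology is an entry condition, baseline in cases falls after biopsy unless blood was taken before eligibility was known.

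**Step 2: how a non-cancer shift appears as discrimination.** Assume a normally distributed marker with equal variance in both groups. Let d_c be its cancer effect among men who were all suspected and biopsied, and d_s the extra shift from suspicion or biopsy, both in SD units. Then:

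- planned contrast: AUC = Φ((d_c + d_s)/√2)
- suspected, biopsied men only: AUC = Φ(d_c/√2)

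All values of d_c and d_s are assumptions.

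| d_c | AUC among biopsied men | Planned, d_s = 0.5 | Planned, d_s = 1.0 | Planned, d_s = 1.5 |
|---|---|---|---|---|
| 0 | 0.50 | 0.64 | 0.76 | 0.86 |
| 0.3 | 0.58 | 0.71 | 0.82 | 0.90 |
| 0.5 | 0.64 | 0.76 | 0.86 | 0.92 |

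For example, with d_c = 0 and d_s = 1.0, Φ(1.0/1.414) = Φ(0.707) = 0.76.

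**Step 3: a second model.** Let a suspicion score be N(0,1) in controls and N(d,1) in cases, with d = 0.3 or 0.545. A standardised marker has correlation ρ with that score and carries no other cancer information. Men above a threshold (0, 0.5 or 1.0) count as suspected. By simulation, suspected cases against suspected controls give an AUC of 0.51 to 0.54. Suspected cases against unsuspected controls give about 0.65 at ρ = 0.3 and about 0.76 at ρ = 0.5. This is an extreme case, because one hard threshold separates the groups completely on the score.

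**Step 4: a force in the other direction.** If a fraction x of controls without histology harbour cancer and resemble the cases, AUC = A(1 − x) + 0.5x. With an assumed A = 0.85:

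- x = 5%: 0.85 × 0.95 + 0.5 × 0.05 = 0.83
- x = 20%: 0.85 × 0.80 + 0.5 × 0.20 = 0.78

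**Step 5: net direction.** With d_c = 0.5, d_s = 0 and x = 20%, the AUC falls from 0.638 to 0.638 × 0.80 + 0.5 × 0.20 = 0.61. With d_s = 0.5 and x = 0, it rises to 0.76. The document supplies none of d_c, d_s or x, so the net direction is open.

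**The case against.** The other side has several good points.

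- **Suspicion is undefined.** Eligibility is normally judged at enrolment, so a man cleared by a negative biopsy may already qualify. A reader might infer that any suspicion, ever, bars a control, or that no control can have been biopsied. The text states neither. This stands, and it means the proposed wording may only clarify the intent.
- **The mechanisms are inferred.** Section 6 never mentions PSA, so a PSA-driven difference is plausible but not documented. Section 4 notes that acute-phase proteins can occur in coronas. Nothing shows that a post-biopsy response is still present at sampling, and an interval may be set in the full protocol. This stands; both routes are assumptions.
- **The exclusion has a purpose.** Without histology, removing suspected men helps keep the control label clean, and should make the contamination in step 4 smaller. This stands.
- **The comparator is reasoned.** Section 6.4 justifies BPH over healthy men by age and benign prostatic disease, and section 6.5 speaks of discovering biomarkers. Comparing confirmed disease with clearly benign controls is a common first-stage design. That defends a discovery study. It does not address suspicion or biopsy status, and it does not support the diagnostic aim of section 6.3.1 or the expectation in section 6.6.

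What survives is the asymmetry in the criteria and the distance between that contrast and the stated use.

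**Conclusion.** The concern holds as a limit on what the first primary endpoint can show. On the plain reading of sections 6.4.1 and 6.4.2, suspicion and biopsy status nearly coincide with case status, and benign men under suspicion are not represented. Apparent discrimination may therefore not carry over to them. Restricting cases to intermediate or high risk, or metastatic, disease widens the gap further.

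A reader might go further and conclude that AUC and specificity are inflated. The document does not support that. The size of the bias cannot be computed from it, opposing forces exist, and every AUC above rests on assumed inputs.

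The treatment-response model for metastatic disease is built within cases and is not affected. The change is worth making because it is cheap and alters what the trial can conclude; it is not a reason to stop a discovery study.

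**What to change.** 1. Reword the section 6.4.2 exclusion to: diagnosis of, or unresolved suspicion of, prostatic neoplasia. Men whose routine biopsy was negative can then enter Subgroup 3.
2. Report specificity separately for biopsy-negative and never-biopsied controls.
3. Record the biopsy-to-blood interval for every biopsied man, case or control. Repeat the analysis excluding men sampled within a prespecified interval after biopsy. Moving the Subgroup 1 draw to a pre-operative visit would not replace this, because that visit is still after biopsy.
4. If the criterion stays as it is, limit the conclusions tied to sections 6.3.1 and 6.6 to discrimination of known intermediate- or high-risk, or metastatic, cancer from unsuspected, clinically diagnosed BPH. Make no claim of early diagnostic accuracy.

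**Cost.** A wording change, one recorded date, a split report and one sensitivity analysis. No biopsy or visit is added. The control population becomes somewhat different, control recruitment is likely to be slower, and the reported AUC will probably be lower.
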